### 6.4.4 Electrocardiograms

The ECG recordings in this clinical trial will be performed by the Investigator or designated nominee. Repeat measurements will be performed if there are any clinically significant abnormalities observed or artifacts are present. All ECG recordings will be reviewed by the Investigator or medically qualified nominee who will document whether the tracing is normal or abnormal. If abnormal the Investigator or medically qualified nominee will document whether the abnormality is assessed as clinically significant or not.

The ECG recordings will be performed once the subject has been resting semi-supine for at least 10 minutes. The following parameters will be reported: QRS, QT, QTc, RR and PR intervals. The formula for calculating the corrected QT interval in respect to the heart rate will also be calculated using either Bazett or Fredericia formulas. If this isn't automatically calculated by the ECG machine, the following formulas will be used:

- Bazett's formula:  $QT / (RR)^{0.5}$   
[Observed QT interval divided by root of RR interval, in seconds]

- Fridericia's formula:  $QT / (RR)^{0.33}$

[Observed QT interval divided by cube root of RR interval, in seconds]

All tracings will be printed out and retained with the subject's source notes. Any clinically significant out of range results will be recorded in the subject's CRF and the subject will be excluded from the study.

#### 6.4.5 Blood and urine samples for laboratory tests

Blood and urine will be collected at Screening (Visit 1), Baseline (Visit 5), and scheduled clinic Visits 7, 9, 16 and 22. Blood will be collected at scheduled clinic Visits 6, 7, 8, 9, 11, 12, 15, 16, 17, 18 and 22. Samples for laboratory tests should be collected within the visit window. Detailed instructions on the handling and processing of specimens are located in the Study Reference Manual. The following will be collected at the times specified in Section 6.3.

|                                 |                                                                                                                                                                                                                                                                                                                                                                |
|---------------------------------|----------------------------------------------------------------------------------------------------------------------------------------------------------------------------------------------------------------------------------------------------------------------------------------------------------------------------------------------------------------|
| Haematology:             | Haemoglobin, haematocrit, red blood cell (RBC) and RBC morphology, white blood cell and differential white blood cell count, platelet count,                                                                                                                                                                                                            |
| Chemistry:               | Sodium, potassium, chloride, bicarbonate, BUN, creatinine, total protein, albumin, lipase, phosphorus, AST, ALT, GGT, alkaline phosphatase, total bilirubin, glucose, CPK, calcium, uric acid, GFR*                                                                                                                                                     |
| Coagulation:             | Prothrombin time (PT), partial thromboplastin time (PTT), and International Normalized Ratio (INR).                                                                                                                                                                                                                                                     |
| Viral Serology:          | HIV, HCV and HBV, HSV-1 and 2 (at screening).                                                                                                                                                                                                                                                                                                           |
| Urinalysis:              | Specific gravity, protein, glucose, blood leukocytes, pH, ketones, bilirubin, urobilinogen, nitrites, protein, and blood..                                                                                                                                                                                                                              |
| Urine pregnancy Testing: | Human chorionic gonadotropin                                                                                                                                                                                                                                                                                                                            |
| Immunological            | Interferon-gamma (IFN<math>\gamma</math>) enzyme linked immunospot (ELISpot) assays (T-cell responses specific for HSV-2 gD2).
ELISA (anti HSV-2 gD2 antibodies)
Exploratory endpoints include measures of humoral and T-cell responses and/or sequencing T-cell receptor gene repertoire and/or sequencing human leukocyte antigen (HLA) gene. |

*\*As determined using the Cockcroft and Gault calculation. Please refer to Section 5.4.2.*

#### 6.4.6 Pregnancy tests

Urine pregnancy testing will be conducted for female subjects at Screening, before administration of each dose of investigational vaccine/placebo and at the end of the study. If positive, a serum pregnancy test will be conducted and the investigational vaccine/placebo will not be administered until the result of this is known. If the result of the serum pregnancy test is negative, administration of study vaccine/placebo will continue. The subject will be re-educated regarding the contraception requirements for this study. If the result of the pregnancy test is positive, the subject will be withdrawn from the study.

#### 6.4.7 Intradermal injection of COR-1 or placebo

Prior to each injection, the forearm(s) that is to be injected will be examined and findings from this examination will be documented. The proposed injection site will be approximately 5 cm below the elbow joint on the inside forearm.

If the subject is allocated to Group 2, that is, to receive 2 injections on the same arm, the second injection site will be located 5 cm away radially, not transversely, from the first injection site. Subject's in Group 2 may choose which arm will be injected, however where possible the non-

dominant arm is preferred. Where possible the same arm will be injected throughout the course of the study.

The skin should be free of blemishes, scars, heavy hair, veins, moles, skin conditions, sores or tattoos that have the potential to interfere with the detection of local reactions.

Areas of skin that involve injection site reactions where possible should be avoided for subsequent vaccinations. Another suitable site should be chosen at least 5 cm away from the existing reaction.

Intradermal injections will be carried out by an individual experienced with ID injections as per Appendix 1.

#### **6.4.8 Photos of injection site (s)**

At Visits 6 and 8, the Investigator or designee will review the subject and inspect their injection sites for evidence of local reactions. If an injection site reaction has occurred, the Investigator or designee the site will take a photo. An injection site reaction is defined as an area of erythema and/or swelling/induration.

At Visits 10, all injection sites will be photographed regardless of whether there is a hypersensitivity type reaction or not.

In addition, if at other times the Investigator or designee assesses an injection site reaction that is unusual and/or not expected, this will also be photographed.

All photographs will be captured in a standardized manner. Please refer to the Study Reference Manual for details of the procedure for image acquisition.

#### **6.4.9 Genital viral shedding assessments**

Subjects will be educated regarding genital swab collection, diary booklet completion and HSV-2 outbreak management. The requirement for compliance in these aspects of the study should be reinforced as often as possible. Additional unscheduled visits may be scheduled for educational purposes should the Investigator or designee judge that this is required.

Daily genital swabs to detect viral shedding will be performed for 45 days commencing as follows:

1. Run-in Shedding Assessment - prior to the first vaccination.
2. Post Vaccination Shedding Assessment - commencing one week following the third investigational vaccine/placebo (Study Period 1); and
3. Post Booster Shedding Assessment - commencing one week after the booster vaccination/placebo (Study Period 2).

Prior to commencing the first assessment period, each subject will be given written gender specific instructions for obtaining genital swabs.

The subject will be instructed to take the swabs at the approximately the same time of the day. Ideally this will be before bathing.

If the subject does not collect a swab at the planned time they will be instructed to obtain a swab as soon as they are able to. (Provided it is on the same day). If this is not until the following day, they will be instructed to document in the diary booklet that a swab wasn't collected, and the reason for not doing so.

Subjects will be given sufficient swabs and courier supplies to enable them to collect the required number of daily swabs. Each subject will receive:

- Swabs,
- Tubes containing the transport medium,
- Spare swabs in case of error,
- Sample biological bags,
- Prepaid/pre-labelled return mail packs,
- Requisition forms;
- Sample labels;
- Torch (for inspection of the genital region);
- Mirror (for inspection of the genital region);
- 'HSV-2 Outbreak' kits for when a subject develops lesions. This kit includes:
  - Swabs;
  - Tubes containing the transport medium,
  - Sample biological bags,
  - Prepaid/pre-labelled return mail packs
  - Requisition Forms; and
  - Sample labels.

Gender specific instructions for obtaining genital swabs will be provided to subjects at Visit 2.

In summary, men will be instructed to obtain the following swabs:

1. Penile skin
2. Perianal and rectal areas.

Women will obtain the following swabs:

1. Vaginal and vulval area;
2. Perianal and rectal areas.

If subjects have previously experienced lesions outside the above mentioned areas, they will be provided with additional swab(s) to enable this region to be swabbed daily providing the lesion is below the waist.

Subjects who do not collect at least 80% of swabs during the Baseline Shedding Assessment (i.e. at least 36 days) will not meet eligibility criteria for the study (see Exclusion criterion 14).

Subjects who test positive for HSV-1 during the Baseline Shedding Assessment will be excluded from this study.

Swabs will be sent directly to the central laboratory each week for analysis. Prior to shipment, the swabs will be kept in the subject's refrigerator in sealed specimen bags.

Should a subject develop an HSV-2 Outbreak during a scheduled 45 day swabbing assessment, the subject should not interrupt this assessment. Additional swabs taken from the lesions will be collected. Please see section 6.4.10.

#### **6.4.10 Diary Booklets**

Subjects will be provided with a diary after each vaccination to collect injection site reactions and at the commencement of each swabbing assessment to collect HSV-2 symptoms.

##### Injection Site Reaction Diary:

---

The aim of this Diary is to collect information about injection site reactions for 7 days following each vaccination. Information that is to be collected includes the presence of:

- Pain/tenderness;
- Swelling/induration;
- Erythema; or
- Other findings.

Subjects will be provided with a ruler to enable the subject to measure and record the size of any injection site reactions that occur in millimetres (mm). Subjects will be instructed to measure the longest diameter of the reaction area. Instructions on the measurement of reactions will be provided to the subjects within their Diary booklet. Injection site reactions will be graded in accordance with the FDA Guidance for Industry document entitled *Toxicity Grading Scale for Healthy Adult and Adolescent Volunteers Enrolled in Preventive Vaccine Clinical Trial* (2007) except for pain and tenderness (see Section 9.2.1).

The Injection Site Reaction Diaries will be issued and collected at the following visits:

- Vaccination 1- Issued at Visit 5, collected at Visit 6;
- Vaccination 2- Issued at Visit 7 and collected at Visit 8;
- Vaccination 3 – Issued at Visit 9, reviewed at Visit 10, and collected at Visit 11; and
- Booster Vaccination/Placebo – Issued at Visit 16 and collected at Visit 17.

When each Diary is returned by the subject, the site staff will check that it is complete and legible while the subject is in the clinic.

#### HSV-2 Symptom Diary:

At the start of each shedding assessment, the subjects will be provided with a Diary to record HSV-2 symptoms. A HSV-2 Symptom Diary will be issued to the subjects at the following time points:

- Visit 2 (Day -45),
- Visit 11 (Week 9), and
- Visit 17 (Week 25).

The subjects will be instructed to inspect the genital region for lesions daily and document each day whether they have experienced any genital herpes symptoms. A mirror and torch will also be provided for this purpose. There are provisions in the Diary to record the presence of:

- Redness;
- Swelling;
- Soreness;
- Itching; or
- Ulceration/blisters.

When each Diary is collected, the site staff will check that it is complete and legible while the subject is in the clinic. Completed diaries will be filed with the source notes.

The Diary Booklets will have provisions for subjects to record concomitant medications and adverse events.

#### HSV-2 Outbreak Diary:

At Visit 2 subjects will be provided with HSV-2 Outbreak Diaries. The purpose of these diaries is to record further information about their HSV-2 outbreak. The site staff will check at each visit that the subject has sufficient blank copies of this diary. Please refer to Section 8.11.

#### 6.4.11 Punch biopsies

The vaccine has been demonstrated to produce a reddened thickening at the site of administration which appears after 24 hours and is maximal at 48 hours. This is characteristic of a delayed type hypersensitivity reaction, which would indicate induction of an appropriate antigen specific cell mediated immune response. However, it could represent some other vaccine induced non-specific or inflammatory response. To establish the nature of the response, immunohistochemistry of the lesion at 48 hours may provide evidence of a T-cell infiltrate, oedema and or a neutrophilic infiltrate which would not be associated with antigen specific immunity).

All subjects who provide written informed consent at Screening will have a skin biopsy taken from the injections site area at Visit 10 for immunohistochemical analysis to assist in determining the type of immune response occurring.

Please refer to Appendix 2 for further information.

#### 6.4.12 Handling and processing of biological specimens

All personnel involved in collecting and handling biological specimens should follow appropriate precautionary procedures for handling biohazardous materials as currently recommended by the national regulatory authority. The processing of all biological specimens will be in accordance with the site's standard practices.

Laboratory safety evaluations, including haematology, clinical chemistry, urinalysis and coagulation will be performed by the sites local laboratory.

Immunological testing will be performed by:

Table 4 – Immunological and Virological Testing Laboratories

|                                   | Laboratory                                         |
|-----------------------------------|------------------------------------------------------------------|
| ELISpot                    | TBA                                                       |
| HSV-2 serology             | TBA                                                       |
| HLA Typing                 | TBA                                                       |
| ICS                        | TBA                                                       |
| Skin biopsy                | TissuPath                                                 |
| Swabs for genital shedding | Victorian Infectious Diseases Research Laboratory (VIDRL) |
| PBMC preparation           | Q-Pharm                                                   |

#### 6.5 Randomisation process

Subjects will first be randomized to one of 2 injection regimens using a 3:1 allocation ratio.

There will be 2 patient groups. Group 1 will be recruited first. Once this group has been fully allocated, Group 2 will open for recruitment.

Group 1 patients will receive one injection to each forearm (i.e. two injections in total at each vaccination) of either:

- Sub-group A: 15 subjects will receive 2 x 500mcg of COR-1;
- Sub-group B: 5 subjects will receive 2 x placebo.

Group 2 patients will receive two injections to the one forearm (i.e. two injections in total at each vaccination) of either:

- Sub-group C: 15 subjects will receive 2 x 500mcg of COR-1;
- Sub-group D: 5 subjects will receive 2 x placebo.

Under no circumstances are the subjects who enrol in this study are permitted to be re-randomised and re-enrolled for a second course of treatment for this protocol.

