| Control Group:     | Placebo to match.                                                                                                                                                                                                                                                                                                                                                                                                                                                                                                                                                                                                                                                                                                                                                                                                                                                                                                   |
| Dosage and regimen | 
All subjects will receive either 2 intradermal injections of 200µL, to the forearm(s).
 
Subjects will be randomised to receive either investigational vaccine or placebo.
 
There will be 2 subject groups. Once Group 1 is fully allocated, Group 2 will then be opened for recruitment.
 
Group 1 patients will receive one injection into each forearm (i.e. two injections in total at each vaccination) of either:
 
 
Group A: 15 subjects will receive 2 x 500mcg of COR-1
 
Group B: 5 subjects will receive 2 x placebo.
 
 
Group 2 patients will receive two injections into the one forearm (i.e. two injections in total at each vaccination) of either:
 
 
Group C: 15 subjects will receive 2 x 500mcg of COR-1
 
Group D: 5 subjects will receive 2 x placebo.
 
 |

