## 4.3 Study Design

This is a randomized single or multi centre, double blind, placebo-controlled, parallel group pilot study to assess the safety and efficacy of a therapeutic HSV-2 DNA vaccine in HSV-2 positive adults. Subjects will be randomized to receive either COR-1 or placebo using a 3:1 allocation ratio. Treatment assignment to either COR-1 or placebo will be double-blinded. There will be 2 Groups of subjects. Group 1 will receive one injection into each forearm. Once this group has been fully allocated, Group 2 will commence recruitment. Group 2 will receive two injections to the one forearm.

There are two primary reasons for inclusion of the 2 placebo arms:

- To maintain the blind; and
- To describe any natural variation in viral shedding rates between the baseline shedding assessment pre- and post-administration of the placebo.

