## 4.4 Dosing Regimens

All subjects will receive either 2 intradermal injections of 200 $\mu$ L, to the forearm(s) of either:

Group 1-

- Two injections each containing 500mcg of COR-1 with one injection in each arm (two injections in total);
- Two injections containing placebo with one injection in each arm (two injections in total).

Group 2-

- Two injections each containing 500mcg of COR-1 in the one arm; or
- Two injections containing placebo in the one arm;

Intradermal injections will be administered to the patient's forearms at 4 weekly intervals. Following this a 6 month booster will administered.

The comparison of one versus two arms is designed to test the effect of antigen presentation of vaccine encoded viral antigens occurring in one draining lymph node (2 administrations in one forearm) versus two draining lymph nodes (one administration to each forearm).

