## **6.6 Blinding**

Since the investigational vaccine is more viscous as compared to the placebo, it will not be possible to blind the study site member who administers the investigational vaccine. The pharmacy team members will also be unblinded. At the commencement of the study, the blinded investigational vaccine administrators will be identified and trained. There will be at least 2 investigational vaccine administrators at each site who have received training in the delivery of intradermal injections. The investigational vaccine administrators will not be permitted to be involved in patient assessments or management throughout the trial. Additionally they will not discuss what they believe the subject is receiving with either the subject or other staff members.

All other site staff and the subject will be blinded to the study treatment, COR-1 or placebo. Admedus Vaccines Pty Ltd and its representatives will also be blinded to the study treatment throughout the course of the study. The investigational vaccine administrator's will make every attempt to ensure that both the subject and the blinded team members do not observe the intradermal injection as this may threaten the integrity of the blind. The subject may place their forearm through a screen which blocks their view or may be asked to turn away during the injection. Similarly site staff will be instructed to not observe the administration of the investigational vaccine/placebo. This will be highlighted during the site initiation visit and throughout the study.

An unblinded monitor will perform drug accountability according to the Monitoring Plan.

The dose and injection regimen will not be blinded.

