## 11 STATISTICAL ANALYSIS

The study is a randomized, double-blind, placebo controlled, Phase I/IIa trial designed as a pilot study whose primary objective is to describe the safety and tolerability of the HSV-2 DNA vaccine COR-1. The study design also includes 2 injection regimen cohorts of: 1) two injections, 500 mcg each, into the same arm, or 2) two injections, 500 mcg each, administered as one injection per arm

Within each injection regimen cohort, subjects will be randomized to receive COR-1 or placebo using a 3:1 allocation ratio. Within each injection regimen, randomization to COR-1 or placebo will be double-blinded. Given the pilot and exploratory nature of the study, the focus of the statistical analysis will be descriptive rather than hypotheses testing. If inferential statistical tests of hypotheses are employed, they will be viewed as exploratory and descriptive rather than confirmatory.

An interim analysis of unblinded immunogenicity and efficacy data is planned. In summary the following available analyses will be performed:

1. Immunogenicity data (ELISPOT and ELISA); and
2. Viral shedding data.

For the analyses, descriptive statistics will be summarized by injection regimen as well as overall. Additional data summaries may include those for a pooled placebo group and/or a pooled COR-1 group. Prior to pooling and to aid in the interpretation, the individual groups contributing to the pooled group will be reviewed to determine how similar or disparate the groups are. The following provides a general overview of the statistical methods. The Statistical Analysis Plan (SAP), will be written and finalized prior to the study blind break and data base lock for both the interim and final analyses.

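### Section 6.5 says the injection regimen is randomised 3:1, but enrolment order sets it, so the one-arm versus two-arm comparison is non-randomised and confounded with recruitment period

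*Protocol*

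**What the plan says.** Section 6.5 (Randomisation process) begins: "Subjects will first be randomized to one of 2 injection regimens using a 3:1 allocation ratio". It continues: "Group 1 will be recruited first. Once this group has been fully allocated, Group 2 will open for recruitment". It then lists sub-groups A (15 on COR-1) and B (5 on placebo) in Group 1, with one injection in each forearm, and C (15) and D (5) in Group 2, with both injections in one forearm. All active subjects receive 2 x 500 mcg.

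The synopsis (Dosage and regimen) has the same sequential rule: "Once Group 1 is fully allocated, Group 2 will then be opened for recruitment". So does Section 4.3: "Once this group has been fully allocated, Group 2 will commence recruitment".

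Section 11 describes a different randomisation from the first sentence of 6.5: "Within each injection regimen cohort, subjects will be randomized to receive COR-1 or placebo using a 3:1 allocation ratio". Section 4.3 also attaches the 3:1 ratio to COR-1 versus placebo.

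Two other places treat the regimen as randomised. Section 11.1.2 plans disposition tables by a regimen it calls randomised, and step 13 of the injection procedure in Appendix 1 speaks of randomisation to same-arm injection.

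On purpose, Section 4.4 says: "The comparison of one versus two arms is designed to test the effect of antigen presentation of vaccine encoded viral antigens", contrasting one draining lymph node with two. Section 6.6 adds: "The dose and injection regimen will not be blinded".

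**The concern.** The opening sentence of 6.5 and the recruitment rule that follows it cannot both be carried out. If Group 2 opens only when Group 1 is full, the date of enrolment determines the regimen and chance plays no part. Someone programming the allocation list, or writing up the trial, could take from 6.5, 11.1.2 and Appendix 1 that regimens were compared at random.

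At stake is how a difference between regimens in local reactions, ELISPOT, ELISA or shedding is read. Such a difference would carry the effect of injection site together with anything else that changed between the two recruitment periods, such as case mix or the addition of sites. Section 4.5 allows the single-centre plan to be revised according to recruitment, and sites added late would fall mainly in Group 2. Nothing in the protocol tells the reader that the comparison named in 4.4 has this limitation. An analysis plan cannot repair it afterwards, because allocation is fixed in the protocol.

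**Working it through.** **Inputs from the protocol.** Sub-group sizes A = 15, B = 5, C = 15, D = 5 (Section 6.5); total 40 (synopsis); ratio 3:1 (Sections 4.3, 6.5 and 11). The protocol gives no SD, effect size, alpha or power, so the results below are in SD units.

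**Step 1: the plan's own figures.**
- Total: 15 + 5 + 15 + 5 = 40. This reproduces.
- COR-1 to placebo within each group: 15:5 = 3:1. This reproduces.
- Regimen split: (15 + 5):(15 + 5) = 20:20 = 1:1. A 3:1 split of 40 by regimen would be 30:10, so the ratio in the first sentence of 6.5 does not reproduce.

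**Step 2: how regimen is assigned.** While Group 1 is filling, the probability of receiving the Group 2 regimen is 0; afterwards it is 1. Regimen and recruitment period therefore coincide. One possible exception is the up to 10 replacements in Section 4.6, whose assignment is not described. A replacement entering Group 1 after Group 2 opens would create slight overlap.

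**Step 3: precision of the two available regimen contrasts.**
- Direct, COR-1 in Group 1 versus COR-1 in Group 2: SE = sqrt(1/15 + 1/15) = 0.365 SD; 95% half-width 1.96 x 0.365 = 0.72 SD.
- Difference of placebo-corrected effects, (A − B) − (C − D): SE = sqrt(1/15 + 1/5 + 1/15 + 1/5) = 0.730 SD; 95% half-width 1.43 SD. The SE is doubled and the variance is four times as large.

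**Step 4: effect of drift (assumed range).** Let d be the shift between recruitment periods, in SD units. The direct contrast is biased by the whole of d. With no true regimen difference, a nominal two-sided 5% test (normal approximation) rejects with probability 1 − Φ(1.96 − d/0.365) + Φ(−1.96 − d/0.365):

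| Assumed drift d | Bias of direct contrast | Rejection of a true null |
|---|---|---|
| 0 | 0 | 5% |
| 0.25 SD | 0.25 SD | 11% |
| 0.5 SD | 0.5 SD | 28% |
| 1 SD | 1 SD | 78% |

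**Step 5: when placebo correction helps.** The mean squared error of the direct contrast is 2/15 + d² = 0.133 + d². For the placebo-corrected contrast, with drift common to both arms, it is 0.533. The two are equal at d = sqrt(0.533 − 0.133) = 0.63 SD. Below that drift the direct contrast has the smaller mean squared error despite its bias.

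**The case against.** The strongest reply is that this is mainly a drafting slip. The synopsis, Section 4.3 and Section 11 give a coherent working design of sequential cohorts with COR-1 and placebo randomised 3:1 in each, and the sub-group sizes in 6.5 agree with it. The trial is an unpowered pilot with descriptive analysis. The primary objective is the safety and tolerability of two regimens compared with placebo, and no listed endpoint is a regimen-versus-regimen contrast. Several features also limit drift: planned recruitment of up to 6 months, one centre as planned, common eligibility criteria, central laboratories for shedding and immunology, scheduled swab training, and baseline-referenced immunogenicity and shedding endpoints.

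Most of this stands, and it limits the consequence. A reader might infer that the trial cannot answer the question its two groups exist for. The documents do not support that: each regimen versus its own placebo remains a randomised comparison and is what the primary objective asks for. A reader might also infer that the placebo-corrected contrast is the only one worth reporting. That fails too. It rests on five placebo subjects per group, lowers mean squared error only if drift exceeds about 0.63 SD, and leaves any treatment-by-period difference in place.

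The reply does not remove the contradiction in 6.5, its echoes in 11.1.2 and Appendix 1, or the unqualified statement of purpose in 4.4. A descriptive regimen difference is confounded just as an inferential one would be.

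**Conclusion.** The point holds. The first sentence of 6.5 is wrong both in the factor it says is randomised and in the ratio it attaches to it. The one-arm versus two-arm comparison is non-randomised and aligned with recruitment period, and the protocol does not say so. COR-1 versus placebo within each regimen is unaffected.

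The allocation arithmetic (20:20, not 30:10) is exact. The size of any bias is unknown. The 11%, 28% and 78% figures are illustrations that rest on assumed drifts of 0.25, 0.5 and 1 SD and a normal approximation; the protocol neither states a drift nor commits to such a test. They show how sensitive the direct contrast would be and do not predict what will happen.

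No reason for the staging is given. Both groups receive the same 2 x 500 mcg, so it is not dose escalation, and the one review point that Section 9 specifies comes before the first booster, not between the groups.

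**What to change.** **If enrolment has not begun:** open both regimens together and randomise concurrently to A:B:C:D at 3:1:3:1, for example in permuted blocks of 8. Five blocks give 15/5/15/5. State a rule for assigning the up to 10 replacements. Delete the sequential opening from the synopsis, 4.3 and 6.5. This keeps the direct contrast at SE 0.365 SD without systematic period bias and needs no extra subjects. The cost is a new list and running both regimens in parallel. The small downside is the loss of informal staging, for which the protocol sets no review gate.

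**Otherwise,** the cost is wording only:
- Replace the first sentence of 6.5 with: COR-1 versus placebo is randomised 3:1 within sequentially enrolled regimen cohorts.
- Align Section 11.1.2 and step 13 of Appendix 1.
- State in 4.3, 4.4 and 6.5 that the regimen comparison is non-randomised.
- Report the direct contrast (SE 0.365 SD) beside the difference of placebo-corrected effects (SE 0.730 SD), noting that the latter removes only drift common to both arms.
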